##### Analysis of the gamified Go/NoGo task

Raw data from the gamified Go/NoGo task will be collected through The Diner smartphone application and preprocessed using the Diner Data Processor, a Matlab-based processor. For each participant, all raw data files will be extracted directly from the smartphone.

Raw log files will then be analysed and transformed into an Excel dataset for each participant through the processor.

Behavioural data will be imported from Excel files to R running or RStudio will be used^59^ and packages from tidyverse.^60^ Mean RTs will be calculated from the correct responses (Hit trials) for each food item, food category, participant and training day. The food category mean RTs will be calculated by averaging the RT of all items within each food category for each participant and day. Overall RT to food cues will be computed by averaging across all food categories, participants and day. In addition, accuracy measures, including the percentage of correct responses, number of errors, and inhibition error rates (FA/CR+FA)*100, will be computed per participant and per day. Further analyses will include modelling using repeated measures analyses of each day.

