#### Go/NoGo gamified task

A specific smartphone will be provided to complete a gamified Go/NoGo task lasting a total of approximately 15 min. Participants will be asked to complete this task 10 times in total; once during each of the visits and nine additional times per visit at home. This task will include 24 randomised food cues of varying fat and carbohydrate content (see section ‘Food categories’) circled in green (Go cues), and 4 randomised object cues circled in red (NoGo cues). In total, there will be 70% of Go cues and 30% of NoGo cues. Participants will complete multiple runs of the task each day until they fulfil a daily objective, receiving intermediate scores after each run, and a final score when the objective is achieved.

Before the first game, participants will be asked in the app to answer a liking questionnaire (Visual Analogue Scale (VAS) from 0=strongly dislike to 100=strongly like), where they will rate food images presented during the Go/NoGo task. Before each task, participants will be asked to answer a questionnaire regarding their current mood (A-MMS), current level of perceived stress (single item) and current level of hunger (single item).

During the task, participants will be instructed to respond as fast as possible to the food cues (Go trials) by sliding the image downward with their finger, while withholding their responses to the non-food cues (NoGo trials). If participants respond to a food cue on time (Hit) or correctly withhold their response to an object cue (correct rejection, CR), positive green feedback will be displayed. If participants fail to respond to a food cue within 1.5 s (Miss) or respond to an object cue (false alarm, FA), negative red feedback will be displayed.

As part of the task’s gamified design, and to maintain engagement and adherence, participants who will correctly respond to food cues but exceed the reaction time threshold (RTT, 725 ms) will receive a negative ‘Late’ feedback, while a ‘Down’ feedback will be displayed if the food cues are not dragged to the bottom of the screen.

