The behavioural output of the gamified Go/NoGo task will include the response type (Hit, CR, FA, Miss), the feedback (Correct, Incorrect, Late, Down), and the individual reaction time (RT) in milliseconds to each food cue. The outcomes will then be analysed in the percentage of successful trials, total number of errors (FA or missed food cue), number of late (Hit with a RT above the RTT), the mean RT (ms) to food cues, mean RT to each food category (HFLC; HFHC; LFLC; LFHC), total mean RT for food cues and inhibition error (proportion of FA relative to the total of FA and CR).

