### Data management and statistical analyses

#### Sample size calculation

The sample size estimation was informed by previous EEG studies of similar design outside of the perinatal context,^23
28
48^ as well as internal pilot data from our group. For EEG outcomes, preliminary data from our previous study (CER-VD 2021-01976) showed a significant fat x group interaction in global field power (GFP) (ηp²=0.103, F(1,37)=4.237, p=0.047; Cohen’s f=0.34). Power analysis assuming an alpha level of 0.05 and 80% power indicated that 35 participants per group were needed. For the Go/NoGo smartphone task used in a different context, pilot data demonstrated group differences in RTs of 550 ms±63 in women with NW and 450 ms±63 in women with OW/OB, at least eight participants per group would be required to detect significant differences in RT assuming an alpha level of 0.05 and 80% power.

Participants diagnosed with GDM at the second visit (approximately 16%) will be excluded in sensitivity analyses. To account for these exclusions and an additional anticipated dropout of 10%–20%, a total of 94 participants (47 per group) with valid data will be recruited. This is expected to result in approximately 37 participants per group at the second visit with valid data, corresponding to the highest requirement derived from our calculations.

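### Two Go/NoGo derivation rules are miswritten: the inhibition-error formula lacks a bracket, and overall food reaction time is averaged across participants

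*Protocol article*

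**What the plan says.** The Protocol article describes the Go/NoGo measures twice.

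- **Go/NoGo gamified task (Measures)** lists the outcomes and defines one of them in words: "inhibition error (proportion of FA relative to the total of FA and CR". It also lists "mean RT to each food category (HFLC; HFHC; LFLC; LFHC), total mean RT for food cues". On the amount of play it says: "Participants will complete multiple runs of the task each day until they fulfil a daily objective".
- **Analysis of the gamified Go/NoGo task** gives the computing rules. For inhibition error: "inhibition error rates (FA/CR+FA)*100, will be computed per participant and per day". For RT, means of correct responses are first formed "for each food item, food category, participant and training day". Category means are then formed by "averaging the RT of all items within each food category for each participant and day". Finally: "Overall RT to food cues will be computed by averaging across all food categories, participants and day".

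The sample size section uses RT in this task for one of its two calculations: "pilot data demonstrated group differences in RTs of 550 ms±63 in women with NW and 450 ms±63 in women with OW/OB", leading to at least eight participants per group.

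**The concern.** The analysis section holds the only computing formula for inhibition error, and that formula does not agree with the definition in words. Anyone who codes it as printed gets a different quantity: an odds plus a count. The count part grows with the number of NoGo trials, and daily play is not fixed in advance but continues until an objective is met. The printed quantity would therefore mix the error rate with the amount of play.

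The overall-RT sentence departs from the two sentences before it. They keep participant and day as separate levels, while this one lists participants among the things averaged over. An RT summary meant for comparing women needs a value for each woman.

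**Working it through.** **The plan's own figure first.** The only computed figure for this task is the 8 per group for RT. Inputs from the sample size section: difference 550 − 450 = 100 ms, SD 63 ms, alpha 0.05 (two-sided assumed), power 80%, equal groups.

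- Normal approximation: n = 2 × (1.96 + 0.8416)² × (63/100)² = 2 × 7.849 × 0.3969 = 6.23, rounded up to 7 per group.
- Two-sample t-test: 7.33, rounded up to 8 per group (power 0.778 at 7, 0.839 at 8).

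The stated 8 reproduces. Neither derivation rule enters it.

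**Inhibition error.**

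- Printed: (FA/CR + FA) × 100. Division precedes addition, so this equals 100 × FA/CR + 100 × FA.
- In words: FA relative to the total of FA and CR, so 100 × FA/(FA + CR).

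If FA ≥ 1 and CR > 0, then FA/CR > 0 and the bracket is greater than 1, so the printed value always exceeds 100%. If CR = 0 it is undefined. If FA = 0 and CR > 0 both forms give 0, the only case in which they agree.

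The article gives no FA or CR counts, so those below are assumed for illustration.

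| FA | CR | Printed, % | In words, % |
|---|---|---|---|
| 0 | 12 | 0 | 0 |
| 1 | 11 | 109.1 | 8.3 |
| 3 | 9 | 333.3 | 25.0 |
| 3 | 27 | 311.1 | 10.0 |
| 6 | 54 | 611.1 | 10.0 |
| 12 | 108 | 1211.1 | 10.0 |
| 12 | 0 | undefined | 100 |

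The rows with 3/27, 6/54 and 12/108 have the same error rate of 10% at 30, 60 and 120 NoGo trials. The definition in words returns 10% each time. The printed form roughly doubles whenever the number of trials doubles.

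**Overall RT.** The three rules in sequence:

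1. Item and category means: kept by participant and training day.
2. Category means: kept by participant and day.
3. Overall mean: taken over categories, participants and day.

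Step 3 read literally leaves a single number, whether 94 women or any other number contribute. Steps 1 and 2 are sound, and a value for each woman and day follows from step 2 directly: (RT for HFHC + RT for HFLC + RT for LFHC + RT for LFLC) / 4.

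**The case against.** The strongest reply is that these are slips in a condensed article and that its own text resolves them. Much of this stands.

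- **The bracket.** The Go/NoGo gamified task section gives a complete definition with the right denominator. The printed formula is called a rate and scaled by 100, which suggests the same percentage was meant. No script is shown, and values above 100% would probably be noticed. A reader might infer that the groups would differ falsely because one plays more runs. The documents do not support that as a prediction: it would need the misprint to be coded as printed and the impossible values to be accepted, and the counts used to show it are assumed.
- **Overall RT.** A reader might infer that no RT per woman is left to compare. That is not so, because the same paragraph keeps item and category means by participant and day. The planned group comparisons, regressions and repeated-measures models also presuppose participant-level data.
- **The sized comparison.** A reader might infer that the RT comparison behind the 8 per group cannot be carried out. The sample size section speaks only of RTs and does not tie the calculation to the overall-RT variable.
- **The primary outcomes.** A reader might infer that a primary outcome is corrupted. The Primary outcomes section names speed and accuracy of responses to the four food categories. False alarms and correct rejections arise on object cues, so inhibition error is not clearly among them, and the category RTs are correctly defined.

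What the reply does not remove is that both sentences state how analysed variables are to be computed, and both give wrong values if followed as printed.

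**Conclusion.** Both rules are wrong as written, and the point is minor. The printed inhibition-error formula contradicts the definition elsewhere in the article, gives more than 100% whenever FA ≥ 1 and CR > 0, and has no value at CR = 0. This follows from the algebra and needs no assumption; only the sizes in the table rest on assumed counts. The overall-RT rule read literally gives one pooled value, and the fault is confined to that summary variable. The category RTs that serve the primary speed outcome and the sample size of 8 per group stand as they are. Whether the processing code carries either error cannot be told from the article.

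**What to change.** In the section on analysis of the gamified Go/NoGo task:

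1. Print the inhibition error rate as 100 × FA/(FA + CR), per participant and day, to match the definition under Measures. Add a check in the processing script that every value lies between 0 and 100.
2. Remove participants from the dimensions over which overall RT is averaged, and say that overall RT is the mean over the four food categories within each participant and day. This keeps the daily values that the planned repeated-measures analyses need.

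The cost is two corrected sentences and one check of the processing code. No extra data, visits or participants are needed, and the sample size does not change.

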## Ethics and dissemination

The study has been approved by the Human Research Ethics Committee of the Canton de Vaud (CER-VD 2023-01462). Written informed consent will be obtained for all participants before any study data are collected. With explicit participant consent, personal medical data (body weight, BMI, body composition, blood pressure, HbA1c) collected during the study visits will be communicated to the participants’ obstetrician or general practitioner in the form of a medical report at the end of their participation.

Once the formal analyses of this study are completed, participants will be invited to a presentation where these will be presented and discussed. Additionally, results will be disseminated by presentations at national and international conferences, publications in peer-reviewed scientific journals, and other scientific meetings.
